### 2.6.2. Secondary outcome measures

|          | Outcome                                                                                                                     | Definition of outcome in ClinicalTrials                                           |
|----------|-----------------------------------------------------------------------------------------------------------------------------|-----------------------------------------------------------------------------------|
| 1 | Treatment with antibiotics initiated within a week (7 days) of the emergency room visit and different groups of antibiotics | Proportion of children with antibiotics in one week                               |
| 2 | Macrolide antibiotics prescribed in the ED                                                                                  | Proportion of children receiving macrolide antibiotic at pediatric emergency room |
| 3 | Macrolide antibiotics started in infants                                                                                    | Proportion of infants aged < 3 months receiving                                   |

|    |                                                                                        |                                                                                                                               |
|----|----------------------------------------------------------------------------------------|-------------------------------------------------------------------------------------------------------------------------------|
|    | under 3 months (proportion)                                                            | macrolide antibiotic at pediatric emergency room                                                                              |
| 4  | Immediate admittance to hospital from emergency room (hospitalized pediatric patients) | Proportion of children admitted to hospital                                                                                   |
| 5  | Hospital admissions within a week after emergency room visit                           | Proportion of children admitted to hospital within one week after study entry                                                 |
| 6  | Other diagnostic tests performed in the emergency room                                 | Number of other diagnostic tests than point-of-care test performed at emergency room                                          |
| 7  | Revisits to emergency room within the next 7 days                                      | Proportion of children admitted to hospital or revisit at emergency room within 7 days after study entry                      |
| 8  | Outpatient phone contacts and their number (with nurse or physician) within 7 days     | Proportion of children with outpatient telephone contact within 7 days after discharge from emergency room                    |
| 9  | Ancillary laboratory testing                                                           | Number of diagnostic tests per child other than point-of-care test performed within one week                                  |
| 10 | Intensive care                                                                         | Proportion of children with admission to pediatric intensive care unit or intensive care unit within 7 days after study entry |
| 11 | Mortality within the next 30 days after the emergency room visit                       | Proportion of children who died within one month after study entry                                                            |
| 12 | Visit associated costs                                                                 | Cost in euros per child per visits                                                                                            |
| 13 | Length of stay at ED                                                                   | Length of stay at emergency room in minutes                                                                                   |
| 14 | Pathogen directed therapy                                                              | Proportion of children receiving correct pathogen directed therapy                                                            |
| 15 | Time from emergency room visit to onset of pathogen-directed treatment                 | Time to initiation of correct pathogen directed therapy                                                                       |

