## **5. ETHICAL CONSIDERATIONS**

To our knowledge, a comprehensive POC test for respiratory tract pathogens is currently not in use in Finnish pediatric clinics and there are no current care guidelines on its use. Intuitively, one might think that more rapid and comprehensive diagnostics would definitely bring benefits to patient care in the form of more accurate diagnostics and shorter treatment times. However, the benefits of routine testing for respiratory pathogens in the emergency room have not been demonstrated in a randomized controlled setting. The benefit of testing must be scientifically evaluated in a university clinic before adoption into routine use.

Pediatric patients seeking emergency treatment for fever and/or respiratory symptoms are recruited to the trial. Because the aim is to achieve a representative data set, no exclusion criteria are determined. The test result is interpreted by the on-call physician; if necessary, after consulting the back-up on-call physician. Patients in very poor condition who require immediate intensive care and whose status does not allow any unnecessary invasive procedures are not recruited to the trial. During the study, the POC device is used for research purposes only; it is not used for emergency room patients who have not been recruited to the study. The study is limited to the emergency room. However, outside the emergency room, doctors in the ICU or hematology ward can order a

POC test on a patient on these wards if they consider that it would be of significant benefit in their care.

Samples for the trial are collected in the same way as in current routine practice. The acute care nurses have a lot of experience of taking samples. The samples taken for the trial are used for diagnosis and for making decisions on treatment during the emergency room visit.

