## **6. CLINICAL RELEVANCE OF THE TRIAL**

Antimicrobial resistance is a growing problem that may in the future endanger the treatment of infections which are currently treatable. To combat antimicrobial resistance, the WHO has published an action plan where one of the strategic aims is optimization of antimicrobial use. Children act as carriers of respiratory pathogens, and as resistant bacterial strains become more common, they also spread them efficiently. Rapid, targeted diagnostics of respiratory pathogens

may help target the use of antimicrobials more precisely and reduce the growth of antibiotic resistance.

The spectrum of microbes that cause acute respiratory infections is wide, and clinically, it is often difficult to tell the difference between bacterial and viral symptoms. However, in terms of treatment, it is crucial to know whether the illness is caused by a virus or bacteria. POC testing of respiratory pathogens sheds more light on the matter. However, the result of a POC test based on nucleic acid detection does not necessarily indicate the presence of a live organism; instead of an infection that can be treated, the finding may be due to colonization, infection with no symptoms, reactivation or prolonged virus shedding, which is why clinical discretion is required when interpreting the results of POC tests. The use of POC testing causes additional costs, but if its use helps reduce the need for additional tests or monitoring in hospital, the total cost of treatment may be lower. A precondition for the rational use of POC tests is that they have an impact on treatment decisions and save cost, and do not put a strain on healthcare resources.

The aim of this trial is to find an additional means of targeting antimicrobial therapy and to demonstrate the clinical benefit and cost-effectiveness of a new microbiological diagnostic test before its more widespread adoption.

The trial also provides additional information about the utilization of POC diagnostics during a pandemic, the prevalence of SARS-CoV2 virus in children, and the need of hospital treatment among pediatric patients requiring assessment in specialized care.

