## 2.5.2. Control group

*Current treatment practice: The diagnostic tests needed are conducted in the laboratory during office hours following a clinical evaluation by the doctor who prescribed the test*

At the moment (since spring 2019), the following tests for respiratory tract pathogens are available in the emergency room of Oulu University Hospital. The tests are done in the laboratory and are prescribed by the on-call physician.

- Nucleic acid detection test for **influenza and RS virus**, analyzed in the laboratory; the results are available **approximately 2–3 hours** after sampling.
- In addition, since 2019, a test covering the most common **respiratory tract viruses as well as mycoplasma and pertussis**, which is done in the laboratory **during office hours** (Qiagen, Table 2)
- For both tests, the sample is most commonly taken from phlegm suctioned from the patient, or from the nasopharynx using a nylon or dacron swab.

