**5.2.6. Diagnostic tests performed in the emergency room**

The average sum of laboratory diagnostic test with 95 % confidence interval will be calculated for each randomization arm. Chest radiographs will be reported as proportion of participants with chest X-ray performed following 7 days after randomization. To analyze the outcome, we will calculate 95 % confidence intervals (CI) of the differences using a Standard Normal Deviate (SND) test for the proportions. Risk ratios (RR) with 95 % CI are calculated.

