#### **5.2.9. Ancillary laboratory testing**

This outcome is defined as the mean count of laboratory tests performed on each participant and proportion of participants with chest X-ray at ED or any radiological imaging within 7 days after study entry. The average sum of laboratory tests will be calculated and reported for each randomization arm. To analyze the outcome, a t-test for continuous valuables with 95 % confidence interval will be calculated. The counts and proportions of participants with chest X-ray at ED of any radiological imaging will be reported. To analyze the outcome, we will calculate 95 % confidence intervals (CI) of the differences using a Standard Normal Deviate (SND) test for the proportions. Risk ratios (RR) with 95 % CI are calculated.

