#### **5.2.12. Visit associated costs**

Total costs related to emergency department visit will be collected. The average sum of costs will be calculated and reported for each randomization arm. To analyze the outcome, a t-test for continuous valuables with 95 % confidence interval will be calculated.

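### The secondary test counts leave out the point-of-care panel but, as worded, not the laboratory respiratory PCRs it may replace; separately, the cost outcome is narrower than the cost objective

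*Combined protocol and SAP*

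**What the plan says.** **Test counts.** SAP 2.6.2 gives two registered definitions. Row 6, for the ED visit, is "Number of other diagnostic tests than point-of-care test performed at emergency room". Row 9, for ancillary testing, is "Number of diagnostic tests per child other than point-of-care test performed within one week". The POC test is the only exclusion in either row.

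The analysis sections are worded differently. SAP 5.2.6 says "The average sum of laboratory diagnostic test with 95 % confidence interval will be calculated for each randomization arm", and SAP 5.2.9 says "The average sum of laboratory tests will be calculated and reported for each randomization arm". Neither repeats the POC exclusion or gives a rule for respiratory PCR in either arm.

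Under SAP 2.5.2, controls may have an influenza/RSV nucleic acid test and a wider respiratory panel, and "The tests are done in the laboratory and are prescribed by the on-call physician". The wider panel is referred to Table 2, which in the protocol lists what the POC device detects. SAP 2.6.3 describes analyses that leave out controls tested for influenza and RSV, so some controls had such tests.

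**Costs.** Protocol 4.1 sets out to compare costs to the health care system. Protocol section 6 reasons that "if its use helps reduce the need for additional tests or monitoring in hospital, the total cost of treatment may be lower". SAP 5.2.12 says "Total costs related to emergency department visit will be collected". The registered definition in 2.6.2, row 12, is per child and per visits, with no time window. SAP 2.10 names the billing database but does not say whether it holds the price of the POC test.

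**The concern.** A count of other tests is a fair downstream outcome if its exclusion covers the same kind of test in both arms. Here it follows where the test is run. Protocol section 2 defines point-of-care testing by its closeness to the patient, so a comparable panel scores zero at the bedside and one in the laboratory. The difference between arms then mixes two things: any change in other testing, which is of interest, and the relocation of the respiratory test itself, which allocation brings about.

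The plan also leaves open which rule the analyst follows. Counting every laboratory test, as 5.2.6 and 5.2.9 allow, may add about one test to each POC child. A reader could be shown fewer or more tests in the POC arm from the same data.

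On cost, an ED-visit total cannot by itself answer a question about health-system cost when one stated route to a saving is less monitoring in hospital.

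**Working it through.** The plan gives no expected test count, SD, PCR rate or unit cost, so there is no figure of its own to reproduce on this point. The sample-size calculation concerns the primary outcome and is not involved.

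**Inputs.**
- q = laboratory respiratory PCRs per control child; r = the same per POC child. Neither is in the documents.
- One counted POC test per POC child. This is a simplification, since failed, repeated and missing samples are foreseen in protocol 4.5 and SAP 4.4.
- No true difference in any other testing.
- 1,350 recruited (protocol 4.5). At 2:1 this is about 900 POC and 450 control.

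**Expected difference, POC minus control.**
- SAP 2.6.2 wording (POC test out, laboratory PCR in): r − q.
- Every test counted: (1 + r) − q.
- Respiratory PCR out of both arms: 0.

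With q = 0.3 and r = 0, these are −0.3, +0.7 and 0 tests per child. Over an assumed range of q from 0.1 to 0.7 and r from 0 to 0.1, the first runs from 0 to −0.7 and the second from +0.3 to +1.0. If r = q, the first is zero.

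**How often this alone would give p < 0.05.** SAP 5.2.9 plans a t-test on the mean count. By normal approximation, with d = q − r:

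SE = SD × √(1/900 + 1/450) = SD × 0.0577, which is 0.115, 0.173 and 0.289 for assumed SDs of 2, 3 and 5.

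P = Φ(d/SE − 1.96) + Φ(−d/SE − 1.96).

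| d | SD 2 | SD 3 | SD 5 |
|---|---|---|---|
| 0.1 | 14% | 9% | 6% |
| 0.3 | 74% | 41% | 18% |
| 0.5 | 99% | 82% | 41% |

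For example, at d = 0.3 and SD 3, d/SE = 0.3/0.173 = 1.73 and P = 41%. The table runs from 6% to 99%, so it shows only that the effect can be negligible or decisive. It does not estimate what happened in this trial. SAP 5.3 makes no multiplicity adjustment, so such a result would be reported at nominal significance.

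**Costs.** No arithmetic is possible. Side by side: the objective is health-system cost (protocol 4.1), the stated routes to a saving are fewer tests or less hospital monitoring (protocol section 6), and the measured quantity is ED-visit cost (SAP 5.2.12). Admissions, revisits and phone contacts to 7 days are outcomes in 2.6.2, but no passage costs them.

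**The case against.** **Control PCRs are not expressly counted.** This stands. That they are counted follows from the literal wording of rows 6 and 9; no passage says so. Section 5 could also be read as silently carrying over the 2.6.2 exclusion, which would remove the conflict between passages but not the uneven exclusion.

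**A built-in advantage for the POC arm.** A reader might infer this, but the documents do not support it. The 2.6.2 wording favours the POC arm only if controls have more laboratory PCRs than POC children. Nothing bars a physician from ordering one for a POC child, for instance after a device failure. Counting every test can push the difference the other way.

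**A laboratory PCR made unnecessary by the bedside result is a real resource effect.** This is fair, and removing PCRs from both arms without showing them would hide it. A separate line per arm keeps it visible.

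**Costs tilted in the same direction.** A reader might infer this too. The ED-visit window is the same in both arms, so leaving out inpatient cost could hide a saving or an excess. Nor do the documents show that the POC price is missing. The statement "During the study, the POC device is used for research purposes only" (protocol section 5) goes on to restrict use to recruited ED patients; it concerns who is tested, not billing. Protocol section 6 itself acknowledges that POC testing brings extra costs.

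**Fewer ancillary tests as a condition for adoption.** Protocol section 6 does not go that far. Its precondition concerns treatment decisions, cost and strain on resources. Fewer tests is one possible route to lower cost.

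**Conclusion.** The point holds for the test counts, as an uneven exclusion combined with analysis sections that do not repeat it. Applied literally, outcomes 6 and 9 carry a component of r − q that is not a change in other testing. Applied as 5.2.6 and 5.2.9 are worded, the component can be 1 + r − q. The two have opposite signs whenever r < q < 1 + r. The actual size is unknown because neither q nor r is given, and the rejection probabilities are illustrative only.

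The cost point holds as a mismatch between the objective and the quantity measured, of unknown direction. It is not an asymmetry between arms, and omission of the test's price is not shown.

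Three secondary outcomes are touched (rows 6, 9 and 12). The primary outcome and the sample size are unaffected.

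**What to change.** **Outcomes 6 and 9.** Exclude every respiratory-pathogen PCR, bedside or laboratory, from the count in both arms. Report these PCRs as a separate line per arm, so that substitution can be seen. Optionally add a total that counts them in both arms. Reword SAP 5.2.6 and 5.2.9 to match.

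**Outcome 12.** State whether the POC unit cost is in the cost data, and add it to each POC child if it is not. Then either report cost per child over 7 days including admissions and revisits, with ED-visit cost as a component, or limit the cost conclusion to the ED visit.

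**Cost of the change.** The counts need SAP wording and some extra derivation from laboratory data that SAP 2.10 describes as already received. The wider cost window needs a further extraction, and the documents do not establish that the database can supply it; including admissions is also likely to widen the confidence interval. Narrowing the conclusion needs only wording.

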### 2.6.3.

#### Explanatory post hoc analyses

During the review process following post hoc- and subgroup analyses were requested and conducted:

797

- 798 1. Days of therapy (DOT), defined as the count of the number of individual antibiotic agents given to a  
799 patient on each calendar day regardless of the number of doses.
- 800 2. The proportion of participants discharged within 90 minutes after admission to emergency  
801 room will be compared.
- 802 3. Subgroup analyses to compare antibiotic prescriptions in the ED excluding those  
803 participants in the control group who underwent testing for influenza and RSV  
804 a. Additional analyses with adjustment for age and sex
- 805 4. Subgroup analyses to compare antibiotic prescriptions in the ED excluding those  
806 participants in the control group who underwent testing for influenza and RSV  
807 a. Additional analysis with adjustment for age and sex  
808

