## 4. MATERIAL AND METHODS

### 4.1. Objective of the trial

The objective of the trial is to investigate whether immediate point-of-care testing of respiratory pathogens in the emergency room improves the treatment of acute pediatric patients compared to diagnostics prescribed by the doctor and conducted in the laboratory. In addition to reduction in antibiotics use, hospitalizations and revisits to the emergency room, the costs to the health care system are compared in the trial.

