**Subjects are recruited for the trial by a pediatric emergency room nurse upon emergency room registration.** The emergency room nurses have previous experience of recruiting patients from two clinical trials. The subjects recruited to the study can also discuss the trial with the on-call physician. The subjects are asked to provide a written consent, after which they are randomized into groups in a 2:1 ratio (treatment under study:current treatment). The interventions are randomized by trial numbers and enclosed in non-transparent envelopes. After asking for consent, the nurse opens the envelope assigned to the number that tells which group the subject is assigned to. Patients randomized to the new treatment practice are asked to give a sample which is analyzed with the POC device in the emergency room. If there are technical problems with the analysis, the nurse may take a new sample if necessary; a note on the technical problem is entered in the device log. During the trial, the number of technical problems with analysis increased, and the device manufacturer was informed of all tests that had failed. During the trial, over a short period from Sep 8 to 28, 2019, an increase in the number of failed samples was observed (9 out of 56, i.e. 16% of all samples analyzed). According to the manufacturer, this was to a significant degree (4 out of 9, 45%) associated with problems with the sample cassette transportation chain and wrong storage temperature during transportation. As technical problems persisted, the operating system of the POC test device was updated on Jan 7, 2020.

If an unforeseen adverse event occurs during sampling, an adverse event report is recorded in the hospital's internal adverse event reporting system; in addition, the investigators are informed of the event. The POC test results are automatically recorded in Weblab and are thus available at the doctor's appointment. Samples are only taken at the on-call physician's discretion from the children randomized to the current treatment group. The samples are stored in the emergency room and transported to the laboratory for analysis at 7 am the next morning. The results are entered into Weblab in the microbiology lab, and the on-call physician is responsible for reporting the results and reacting to them.

Due to the SARS-CoV2 epidemic and change in testing practices, randomization was halted on March 13, 2020 at 3 pm when 1,350 subjects had been recruited.

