847 Due to the current pandemic, the statistical power was calculated based on the data about antibiotic  
848 consumption in study population to decide whether to complete or discontinue the study due to Covid-19  
849 pandemic. On Feb 18, 2020, in the study database, antibiotics had been prescribed in 30.4% of children  
850 (about 700 children). No interim analysis was performed. At the time it was estimated that the proportion  
851 of children with antibiotic prescriptions would be higher in the control group, about 33%. By using the  
852 baseline proportion 33% in the control group, and with the same relative reduction of 25%, we calculated  
853 the final sample size.

854

855 A new calculation of the sample size required was made (Feb 18, 2020) using StatsDirect 3:

856

857 Sample size for independent cohort study

858

859 Probability of event in control group = 0.33

860 Probability of event in experimental group = 0.25

861 Controls per case subject = 0.5

862 Alpha = 0.05

863 Power = 0.8

864

865 For uncorrected chi-square test: N = 747 case subjects and 373 controls

866 For corrected chi-square and Fisher's exact tests: **N = 785 case subjects and 392 controls (1177**  
867 **children in total)**

868

869 Missing data were rare due to comprehensive medical records in the hospital and in the national registers.  
870 **Based on the calculation, the sample size reached was considered sufficient in terms of statistical power**  
871 **even if the randomization had to be stopped prematurely.**

872

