## **5 COMPARATIVE ANALYSES**

For all outcomes, the primary analysis will be performed on the intention to treat (ITT) population. Pairwise comparisons for each outcome between randomization arms will be reported.

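### SAP 2.6.3 items 3 and 4 remove only the control children who had a physician-ordered influenza/RSV test, so this post hoc comparison of ED antibiotics is not between randomised groups

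*Combined protocol and SAP*

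**What the plan says.** SAP 2.6.3 introduces its list with the words "During the review process following post hoc- and subgroup analyses were requested and conducted". Items 3 and 4 both compare ED antibiotic prescribing, which is the primary outcome, after excluding "participants in the control group who underwent testing for influenza and RSV". Each has a sub-item adding adjustment for age and sex. The two items differ only in a singular against a plural in that sub-item.

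SAP 2.5.2 describes how controls come to be tested. The on-call physician prescribes the influenza/RSV test after seeing the child, the laboratory runs it, and "the results are available approximately 2–3 hours after sampling". Protocol 4.5 says of sampling in this arm: "Samples are only taken at the on-call physician's discretion from the children randomized to the current treatment group". By then consent has been given and the allocation envelope opened. In the POC arm the sample is taken at registration (protocol 4.4, SAP 2.5.1).

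The main analysis is stated in SAP 5: "For all outcomes, the primary analysis will be performed on the intention to treat (ITT) population". The objective in protocol 4.1 is POC testing "compared to diagnostics prescribed by the doctor and conducted in the laboratory".

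**The concern.** The motive for the exclusion is easy to see. Some controls had a fairly quick viral result, and a reviewer could reasonably ask what POC testing does against children who had none. But the rule removes children according to a clinical decision made after randomisation, and in one arm only. A physician may order the test because the illness looks viral or because the child looks unwell, and either reason can also bear on whether antibiotics are given. Appendix 1 of the protocol itself tells clinicians to weigh general condition and C-reactive protein. Neither is in the adjustment.

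What is at stake is how items 3 and 4 are read. They could be taken as a purer estimate of the effect of POC testing, when selection alone can move the figure. The trial's main answer is not at stake.

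**Working it through.** **Step 1: the rule, arm by arm.**

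| | POC arm | Control arm |
|---|---|---|
| Who is sampled | Children in the arm, at registration | Those the on-call physician chooses |
| When that is settled | By allocation | After allocation, on clinical evaluation |
| Removed under items 3 and 4 | Nobody | Children tested for influenza/RSV |
| Those who would be tested under usual care | Kept | Removed |

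A subgroup analysis applies one restriction to both arms. This one cannot, because the plan describes no record of which POC children would have been tested under usual care.

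**Step 2: the shift this produces.** The SAP gives no figure for these items, so there is none to reproduce. Let p be the antibiotic proportion among all controls, q the share of controls tested, and t the antibiotic proportion among those tested. Then

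- proportion in retained controls = (p − q·t) / (1 − q)
- shift from p = q·(p − t) / (1 − q)

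The shift is zero only when q = 0 or t = p. Its sign is the sign of p − t. Retained controls look worse if tested children got fewer antibiotics, and better if they got more.

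**Step 3: inputs for an illustration.**

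- p = 0.304 in both arms, with no true effect. SAP 2.8 reports that "antibiotics had been prescribed in 30.4% of children" in the study database, without splitting by arm. Using it for both arms is an assumption.
- 900 POC and 450 control children. This is the 1,350 at which recruitment stopped (protocol 4.5: "randomization was halted on March 13, 2020 at 3 pm when 1,350 subjects had been recruited") divided 2:1. The actual arm sizes are not given.
- q = 0.20, and t between 0.25 and 0.35. Both are assumed; the documents give neither.

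**Step 4: results.** With q = 0.20, 90 controls are removed and 360 remain.

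- t = 0.25: (0.304 − 0.050)/0.80 = 0.3175. Risk ratio 0.304/0.3175 = 0.96; difference −1.35 points.
- t = 0.304: (0.304 − 0.0608)/0.80 = 0.304. Risk ratio 1.00; difference 0.
- t = 0.35: (0.304 − 0.070)/0.80 = 0.2925. Risk ratio 0.304/0.2925 = 1.04; difference +1.15 points.

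If the SND test of SAP 5.1 were applied to these comparisons, the false-positive rate would be about 7-8% at the two ends, against a nominal 5%. That is conditional, because SAP 5 names no test, effect measure or adjusted model for items 3 and 4.

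**The case against.** The strongest reply is that nothing in the trial depends on these items. They are declared post hoc, they lie outside the primary and secondary outcomes, SAP 2.7 frames hypotheses only for those outcomes, and the analyses had been carried out when the text was added (SAP version 7.0, 29 March 2022). All of this is correct, and it is why the point is minor. It does not remove the defect. A post hoc label warns about timing and multiplicity, and tells the reader nothing about lost comparability. Calling the items subgroup analyses suggests that the groups are still randomised.

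A second reply is that the size is assumed throughout. That also stands. A reader might infer that the exclusion makes a spurious significant result likely. A false-positive rate near 30% can be produced, but only by assuming that 30% of controls were tested and that their antibiotic rate lies about 10 points from the overall 30.4%. The documents support neither figure, and they equally allow no bias at all.

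Third, the repeated item is probably a copying slip. It is an editorial matter and adds no weight to the selection argument.

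**Conclusion.** Wrong as written, and minor. Items 3 and 4 set a complete randomised arm against controls selected by a post-randomisation clinical decision, and adjustment for age and sex does not make the two comparable. This conclusion rests on the text alone.

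The direction and size of the bias cannot be determined from the documents. Under the assumed middle values the risk ratio is 0.96 to 1.04 with no true effect, a shift of little more than one percentage point either way. For scale, the revised sample size in SAP 2.8 was planned on 8 points (33% against 25%).

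Two stronger readings should be resisted. One is that the trial's main result is compromised. It is not: ITT keeps every randomised child, and the comparator in the objective is doctor-ordered laboratory testing, which includes the influenza/RSV test. The other is that the exclusion is known to favour POC testing. Nothing in the documents says whether tested controls received more or fewer antibiotics than the rest.

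**What to change.** Keep the ITT comparison as the only effect estimate for ED antibiotic prescribing. If the requested exclusion is still shown:

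- call it a non-randomised comparison and say why: testing was the physician's decision after allocation, and the restriction applies to one arm;
- report how many controls were excluded, their baseline features and their antibiotic proportion, so that a reader can put real values of q and t into the formula above;
- give no P value and draw no effect conclusion, with or without the age and sex adjustment.

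Delete item 4, or state how it differs from item 3 if another analysis was meant.

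The cost is a few sentences and one short descriptive table. SAP 2.10 already provides for the antibiotic and laboratory-test data, so no new data collection should be needed. What is given up is a formal estimate against untested controls, which this exclusion could not validly supply.
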